# The TRACTISS Protocol: a randomised double blind placebo controlled clinical TRial of Anti-B-Cell Therapy In patients with primary Sjögren’s Syndrome

**DOI:** 10.1186/1471-2474-15-21

**Published:** 2014-01-17

**Keywords:** Sjögren’s syndrome, Rituximab, Anti-B-cell, Double-blind, Placebo, Trial

## Abstract

**Background:**

Primary Sjögren’s Syndrome (PSS) mainly affects women (9:1 female:male ratio) and is one of the commonest autoimmune diseases with a prevalence of 0.1 – 0.6% of adult women. For patients with PSS there is currently no effective therapy that can alter the progression of the disease. The aim of the TRACTISS study is to establish whether in patients with PSS, treatment with rituximab improves clinical outcomes.

**Methods/design:**

TRACTISS is a UK multi-centre, double-blind, randomised, controlled, parallel group trial of 110 patients with PSS. Patients will be randomised on a 1:1 basis to receive two courses of either rituximab or placebo infusion in addition to standard therapy, and will be followed up for up to 48 weeks. The primary objective is to assess the extent to which rituximab improves symptoms of fatigue and oral dryness. Secondary outcomes include ocular dryness, salivary flow rates, lacrimal flow, patient quality of life, measures of disease damage and disease activity, serological and peripheral blood biomarkers, and glandular histology and composition.

**Discussion:**

The TRACTISS trial will provide direct evidence as to whether rituximab in patients with PSS leads to an improvement in patient symptoms and a reduction in disease damage and activity.

**Trial registration:**

UKCRN Portfolio ID: 9809 ISRCTN65360827.

## Background

Primary Sjögren’s Syndrome (PSS) mainly affects women (9:1 female:male ratio) and is one of the commonest autoimmune diseases with a prevalence of 0.1 – 0.6% of adult women in community studies using the American-European Consensus Group (AECG) criteria [1-3]. PSS is characterised by a combination of features including oral and ocular dryness, which can be disabling symptoms, ocular signs i.e. objective evidence for ocular involvement, abnormal appearance of salivary glands, salivary gland involvement and presence of antibodies to Ro and/or La. PSS patients may also experience severe, variable & unpredictable fatigue, which is similar in character and severity to that of patients with Systemic Lupus Erythematosus (SLE) [4]. Similarly, fibromyalgia (widespread chronic pain, unrefreshing sleep and 11 out of 18 tender trigger points) is found in 5% of PSS patients, again comparable to SLE [4]. Organ-specific systemic involvement is observed in 5-20% of patients. This includes rashes, peripheral neuropathy, non-erosive arthritis, interstitial cystitis, lung and renal disease. These patients almost always have evidence of B-cell hyper-reactivity with anti-Ro/La antibodies & hypergammaglobulinaemia.

For patients with PSS there is currently no effective therapy that can alter the progress of the disease. Symptomatic therapies for dry eyes, such as artificial tears, are reasonably effective. By contrast, therapies for dry mouth (sprays, gels or lozenges/pastilles) are poorly effective for most people. There is no effective therapy for fatigue.

Hydroxychloroquine and/or low dose prednisolone are often used in mild disease. At the severe end e.g. progressive neuropathy, IV methylprednisolone, cyclophosphamide, azathioprine, ciclosporine, mycophenolate or chlorambucil may be used.

Rituximab (MabThera®/Rituxan®) is a chimeric mouse/human monoclonal antibody against human CD20, a non-glycosylated transmembrane phosphoprotein, expressed on pre-B and mature B-lymphocytes. Rituximab depletes B cells by several potential mechanisms, including complement-mediated lysis, antibody-dependent cellular cytotoxicity (ADCC)-mediated killing, and apoptosis. Treatment with rituximab induces a rapid and sustained depletion of B cells. Median peripheral B-cell counts decline below normal following completion of the first dose, with recovery beginning after 6 months. B-cell levels return to normal between 9 and 12 months following completion of therapy.

Rituximab is currently approved for the treatment of relapsed or refractory non-Hodgkin’s lymphoma (NHL), chronic lymphocytic leukemia (CLL), and in combination with methotrexate (MTX) for the treatment of Rheumatoid Arthritis (RA) patients who inadequately respond to one or more anti-tumor necrosis factor (anti-TNF) therapies.

There is supportive evidence for the beneficial effects of rituximab in treating PSS patients from several small studies [5-10]. There is also early data that in patients with high pre-treatment levels of B-cell Activating Factor/B Lymphocyte Stimulator (BAFF/BLyS), B-cell recovery occurs sooner [11] following rituximab therapy and also that BAFF/BLyS levels increase following B-cell depletion [12]. A multicentre parallel-group randomised double-blind placebo controlled study of rituximab in 120 patients with PSS in France has completed [13]. In this study patients were randomly allocated to receive one course of rituximab or placebo infusions at weeks 0 and 2, with follow-up at 24 weeks. The primary outcome was a 30 mm improvement in two out of four visual analogue scales (VAS – Range 0-100 mm) (patient global assessment of disease activity, joint pain, fatigue and dryness) at 24 weeks. Preliminary results of the trial reveal that it failed to meet its primary endpoint over the 24 week period, potentially suggesting that the TRACTISS trial is justified in assessing the efficacy of two courses of treatment, each with two doses, spaced two weeks apart which is in contrast to the French trial which administered only one course of two doses. Furthermore, the TRACTISS trial is intended to be closely aligned to the design of the French study to permit a meta-analysis. As a consequence the eligibility criteria and potential impact on patient recruitment was modelled from data in the United Kingdom Primary Sjögren's Syndrome Registry (UKPSSR) [14] to ensure a robust recruitment strategy could be employed.

T-cell phenotypes and transcriptional profiles have been reported to be abnormal in the peripheral blood and affected tissues of patients with PSS, where T cells comprise the majority of infiltrating lymphocytes. B cells and T cells interact in lymphoid organs and within the inflamed tissue, suggesting that any clinical effects of B-cell depletion may be due to indirect effects on T cells. In a subset of patients in TRACTISS, T cells will be isolated from peripheral blood and their transcriptional profiles compared to healthy and disease controls to explore whether abnormal T-cell transcriptional activity at baseline (a) normalises following Rituximab therapy; and (b) predicts the patients’ subsequent clinical course. The results will also be compared with transcriptional activity of lesional T cells in an attempt to find peripheral blood correlates of T cell-mediated damage to lesional tissue.

PSS imposes a cost burden on patients and the health service. Annual direct healthcare costs of PSS have been estimated at £2,188 per annum per patient, comparable to a cost of £2,693 per annum per patient for those with RA [15]. Although this study predated the widespread use of biologic therapy in RA it suggests that treating PSS currently costs 50-80% of the total cost of treating an RA patient and further supports the observation that untreated PSS has a significant health economic impact.

## Methods/design

### Trial aims and objectives

The main aim of the study is to determine whether use of rituximab is of benefit to patients with PSS.

### Primary objective

To assess whether rituximab, compared with placebo infusion, improves symptoms of fatigue and oral dryness measured by visual analogue scales (VAS) in patients with PSS.

### Secondary objectives

To assess whether rituximab, compared with placebo:

• Increases salivary and lacrimal flow.

• Produces improvement in serological and peripheral blood inflammatory features.

• Improves quality of life and disease activity indices.

• Produces improvement in systemic features.

• Is cost effective.

To further validate questionnaires measuring disease activity and patient symptoms currently in development for use in the assessment of Sjögren’s Syndrome.

### Sub-studies objectives

To conduct a central analysis of local and systemic T-cell abnormalities in patients with PSS and their response to B-cell depletion:

• To compare peripheral blood T-cell transcriptional signatures in PSS patients with healthy and disease controls.

• To compare peripheral blood T-cell transcriptional signatures in PSS patients’ pre- and post- B-cell depletion.

• To characterise tissue distribution, phenotype, and gene expression of lesional T-cells in PSS patients pre- and post-B-cell depletion.

#### Optional labial gland biopsy and imaging

• To conduct a central review to assess whether rituximab has an effect on glandular histology and to determine whether ultrasound imaging is an effective tool in determining treatment response.

### Trial design

The TRACTISS trial is a multi-centre, double-blind, randomised, controlled, parallel group trial in 110 patients with primary Sjögren’s Syndrome exhibiting both fatigue and oral dryness to evaluate the use of two courses of rituximab compared to placebo infusion, in addition to standard therapy. Patients will be followed-up for up to 48 weeks (see Figure 1).

**Figure 1 F1:**
[figure not shown]
TRACTISS trial flow diagram.

### Recruitment

Participant recruitment is planned over a 36-month period from a maximum of 25 centres across the United Kingdom. Patients will be approached by a research clinician during standard clinic visits. Alternatively patients may be identified by case note review and the UKPSSR and sent a Patient Invitation Letter inviting them to take part. Patients will be provided with verbal and written details about the trial (detailed Patient Information Sheet). Patients will be given at least 24 hours to read the information to consider participation. Patients will be invited to provide written informed consent before being formally assessed for eligibility by the Principal Investigator or any other qualified member of the trial team. Eligible patients from centres that have access to ultrasound and also have the facilities to perform gland biopsies will be invited to take part in the optional sub-studies to obtain minor labial gland biopsies and labial salivary gland ultrasound scans.

### Screening

Patients will be registered for the study before any trial-related invasive or non-invasive procedures are performed. All patients will undergo a screening assessment within 28 days prior to the start of treatment to determine eligibility for the study. Patients need to satisfy all of the study inclusion criteria and not have any of the exclusion criteria in Table 1. Patients who are initially ineligible for the trial may be re-screened at a later date. This applies to patients with low or no salivary flow, have no systemic features (but have disease duration of 10+ years) or have a fatigue and/or oral dryness rated as below 5 on a Likert scale of 0–10.

**Table 1 T1:** Eligibility criteria for randomisation into the TRACTISS trial

**Inclusion criteria**	
1	Aged between 18 and 80 years of age.
2	A confirmed diagnosis of primary Sjögren’s Syndrome by AECG criteria.
3	Positive for anti-Ro auto-antibodies.
4	Patients with a diagnosis of primary Sjögren’s Syndrome (by AECG criteria) with more than 10 years disease duration must have at least one systemic feature of*:*
	• Hypergammaglobulinaemia (IgG over 16)*, or
	• Low complement C4*, or
	• Cryoglobulinaemia
	**OR**
	• Active/past history since diagnosis of the following (ascribed to Sjögren’s Syndrome):
	○ Purpura/cutaneous vasculitis,
	○ Lymphadenopathy,
	○ Persistent parotid salivary gland swelling not due to infection,
	○ Peripheral neuropathy (previously documented by nerve conduction tests),
	○ Interstitial lung disease confirmed by HRCT,
	○ Renal tubular acidosis requiring treatment,
	○ CNS disease ascribed to Sjögren’s syndrome (confirmed by MRI),
	○ Myositis (CPK>2N and EMG or biopsy evidence of myositis),
	○ Inflammatory arthritis
5	An unstimulated salivary flow rate greater than 0 ml in 15 minutes.
6	Symptomatic oral dryness (≥ 5/10 on patient-completed Likert**).
7	Symptomatic fatigue (≥ 5/10 on patient-completed Likert**).
8	Patients on corticosteroids, NSAIDS, antidepressants, DMARDs (e.g. methotrexate, hydroxychloroquine, azathioprine, MMF, leflunomide, ciclosporin etc.), or pilocarpine*** must have been on a stable dose for 4 weeks prior to receiving the first infusion of study medication and expected to remain on this dose throughout the study. If they have stopped any of these drugs they should have been off it for at least 4 weeks prior to receiving study medication.
9	Given their written informed consent to participate in the trial and expected to be able to adhere to the study visit schedule and other protocol requirements.
	*Anti-Ro antibody test, IgG, RF and C4 assays performed within 6 months of screening may be used to confirm eligibility. If greater than 6 months repeats should be performed locally at screening to confirm eligibility.
	**LIKERT range 0-10 with 10 corresponding to worst severity.
	***Pilocarpine or drugs with similar pharmacological action should not be used within 12 hours of the assessment visits at screening, baseline, week 16, week 24, week 36 and week 48 (end of study).
**Exclusion criteria**	
	Patients will be excluded from the trial for the following reasons:
1	Diagnosis of secondary Sjögren’s Syndrome.
2	Pregnancy, lactation or women of child-bearing potential (WCBP) unwilling to use medically approved contraception whilst receiving treatment and for 12 months after treatment has finished.
3	Men whose partners are of child-bearing potential but who are unwilling to use appropriate medically approved contraception whilst receiving treatment and for 12 months after treatment has finished.
4	Patient has active or prior hepatitis B or C, known HIV positivity or known history of tuberculosis.
5	Immunodeficiency or neutropaenia <1.5 × 10^9^/l (unless a diagnosis of benign ethnic neutropaenia has been confirmed in which case the neutrophil count must be > 0.9 × 109/l at screening for Jamaican and Afro-Caribbean populations [16]).
6	Any AECG exclusion criteria not covered elsewhere (graft versus host disease, primary lymphoma excluding PSS, sarcoidosis).
7	Any malignancies that would normally preclude the use of rituximab within the past 5 years, including solid tumours, haematological malignancies and carcinoma in situ (except basal cell or squamous cell carcinoma of the skin that has been excised and cured).
8	Participation in a clinical study involving administration of an investigational drug within the past 4 weeks prior to the first infusion.
9	A history of major surgery within 3 months prior to first infusion or planned surgery during the study.
10	Receipt of live/attenuated vaccine within 4 weeks prior to the first infusion.
11	Previous exposure to rituximab or any other monoclonal antibody within the past 5 years.
12	History of recurring or chronic infections or underlying conditions which may further predispose patients to serious infection.
13	History of moderate to severe congestive heart failure according to the New York Heart Association (NYHA) functional classification system or other uncontrolled heart disease, or who have a clinically significant abnormal ECG at the time of screening.
14	History of receiving human/murine recombinant products or known allergy or anaphylactic reaction to a biologic agent or any component of the active substance or any of its excipients or murine components.
15	Patients with fibromyalgia or a diagnosis of significant depression or anxiety that in the opinion of the clinician would confound the interpretation of the study results.
16	Current or a history of severe, progressive or uncontrolled renal, hepatic, hematologic, gastrointestinal, endocrine, pulmonary, cardiac, neurologic, or cerebral disease (including demyelinating diseases such as multiple sclerosis).
17	Any history of organ transplant (with the exception of a corneal transplant >3 months prior to study entry).
18	Presence of a clinically significant illness or mental disorder within 4 weeks of the start of the trial where the safety of the individual might be at risk by entry into the trial, or where the individual does not have the capacity to consent or where the outcome of the therapy cannot be assessed by virtue of the illness or disorder. Each patient will be assessed individually and no person who wishes to participate will be unreasonably excluded by virtue of the illness or disorder.

### Randomisation

Following confirmation of eligibility, patients will be randomised on a 1:1 basis to receive either rituximab or placebo infusion, in addition to standard therapy. Randomisation will be performed using minimisation incorporating a random element, to ensure treatment groups are well-balanced for: Centre; Age (≥65 or <65); Disease Duration (≥10years or <10years); Consent for minor labial gland biopsy; Consent for ultrasound scan. Both registration and randomisation will be performed centrally using an automated 24-hour telephone system based at the Leeds Clinical Trials Research Unit.

Participating research sites will be required to complete a log of all patients over the age of 18 with PSS who are not registered for screening nor randomised either because they are ineligible or because they decline participation.

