#### Primary outcome analyses

A binary logistic regression approach will model the odds of achieving a 30% reduction in symptoms for patients receiving rituximab compared to placebo. Models will include baseline scores for oral dryness and fatigue, as well as disease duration (≤10 years/>10 years), age and centre. The estimated odds ratio for treatment effect will be presented, with the associated 95% confidence interval, and p-value from a likelihood ratio test comparing the models with and without the treatment variable. In addition, the number and proportion of patients in both the rituximab and placebo groups who achieve a reduction in either oral dryness or fatigue >30% between the end of study visit (week 48) and the baseline visit will be summarised. Multiple imputation will be used to impute missing primary endpoint data.

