#### Secondary outcome analyses

• Fatigue, oral and ocular dryness, patient and physician global assessments: For each symptom, a multi-level repeated measures linear regression model will be used to compare VAS scores between groups, models will include the minimisation factors (age, centre, disease duration).

• Salivary and Lacrimal Flow: The flow rates (stimulated salivary flow, unstimulated salivary flow, lacrimal flow) will be compared between the treatment groups using a multi-level repeated measures linear regression model, models will include the values at baseline and the minimisation factors.

• Quality of Life and Disease Activity Indices: The change in each Quality of Life Score, from baseline to 24 and 48 weeks, as measured by SF-36 and each Disease Activity Index (ESSDAI, ESSPRI, SF-36 and PROFAD-SSI) will be compared between treatment groups using a linear regression model, including baseline score values and the minimisation factors.

• Safety and toxicity: Safety analyses will summarise the adverse events (including serious adverse events (SAEs), serious suspected adverse reactions and suspected unexpected serious adverse events), laboratory changes and treatment-related mortality rates. Safety data will be presented by treatment group and relationship to study treatment or underlying PSS. Expected SAEs related to rituximab include infusion-related reactions, infections, cardiovascular events, hepatitis B reactivation and Progressive Multifocal Leukoencephalopathy.

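### The covariates in the models do not match the minimisation: disease duration is cut on the other side of 10 years, and two of the five factors are left out without explanation.

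*Protocol article*

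**What the plan says.** All places are in the protocol article.

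- **Randomisation.** Allocation is 1:1. "Randomisation will be performed using minimisation incorporating a random element", "to ensure treatment groups are well-balanced for: Centre; Age (≥65 or <65"), and then "Disease Duration (≥10years or <10years); Consent for minor labial gland biopsy; Consent for ultrasound scan". That makes five factors, with exactly 10 years in the upper duration group.
- **Primary outcome analyses.** "Models will include baseline scores for oral dryness and fatigue, as well as disease duration (≤10 years/>10 years), age and centre". Exactly 10 years now falls in the lower group, and neither consent factor appears.
- **Secondary outcome analyses.** For the symptom scales and global assessments, "models will include the minimisation factors (age, centre, disease duration"). The bullets on flow rates and on quality of life and activity indices refer to the minimisation factors without listing them.
- **Eligibility.** Inclusion criterion 4 in Table 1 says that patients "with more than 10 years disease duration must have at least one systemic feature of" a given list. The Screening section, describing who may be re-screened, mentions patients who "have no systemic features (but have disease duration of 10+ years").

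**The concern.** Minimisation makes the arms alike on its factors by design. The usual way to let the analysis reflect this is to adjust for the same factors, coded as they were at allocation. Here two specifications written out in the same article disagree on the coding of one factor and on how many factors there are. An unseen analysis plan cannot make the two published lists agree.

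There are two practical consequences. First, the duration covariate in the primary model is not the variable that was balanced. Second, the secondary models are ambiguous: one analyst could fit three factors and another five, and both could claim to follow the text. What could be lost is some precision and power, together with certainty about the covariate set behind the primary odds ratio and its likelihood ratio test.

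**Working it through.** **Step 1. Set the lists side by side.**

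| Factor | At minimisation | Primary model | Secondary models (first bullet) |
|---|---|---|---|
| Centre | yes | yes | yes |
| Age | ≥65/<65 | yes, form not given | yes, form not given |
| Disease duration | ≥10/<10 years | ≤10/>10 years | yes, cut not given |
| Biopsy consent | yes | no | no |
| Ultrasound consent | yes | no | no |

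Five factors are used at allocation, three are carried forward, and 5 − 3 = 2 are left out. The form of age is a detail that an analysis plan can settle, so it is not counted here.

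**Step 2. Who is affected by the duration cut?** Only patients recorded at exactly 10 years: they satisfy ≥10 at allocation and ≤10 in the model. The article does not say how finely duration is recorded. If it is calculated from dates, almost nobody sits on the boundary. If it is recorded in whole years and 3% to 8% of patients are at 10 (an assumption), the number is 0.03 × 110 = 3.3 to 0.08 × 110 = 8.8.

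**Step 3. Check the design figure.** The inputs from the Sample size section are 25% versus 55%, two-sided 5% and 50 evaluable per group. The normal-approximation formula with continuity correction gives 48 per group, so 50 is adequate for the stated 80%. On the log odds scale used by the primary model:

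- log OR = ln[(0.55/0.45)/(0.25/0.75)] = ln 3.67 = 1.299
- SE = √[1/(50 × 0.25 × 0.75) + 1/(50 × 0.55 × 0.45)] = √(0.1067 + 0.0808) = 0.433
- power = Φ(1.299/0.433 − 1.96) = 85.1%

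**Step 4. Power forgone by omitting a balanced factor.** Assume one binary factor with 50% prevalence, exactly balanced between arms, with the overall response rates kept at 25% and 55%. The adjusted SE comes from the information matrix of the logistic model with treatment and factor.

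| Factor's odds ratio for outcome | Adjusted treatment OR | Adjusted log OR | Adjusted SE | Power adjusted | Power unadjusted |
|---|---|---|---|---|---|
| 1 | 3.67 | 1.299 | 0.433 | 85.1% | 85.1% |
| 2 | 3.80 | 1.335 | 0.441 | 85.7% | 85.1% |
| 3 | 4.02 | 1.391 | 0.453 | 86.6% | 85.1% |

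Adjusting raises the SE, but it moves the estimate further from the null by more. Omission therefore shows as an attenuated odds ratio and a small loss of power: about 0.6 points at an odds ratio of 2 and 1.5 points at 3.

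**Step 5. Type I error with the factor omitted.** This used 100,000 simulated trials with 50 per arm, 25% response in both arms, the same balanced factor, and a likelihood ratio test against 3.841. The rejection rates were 5.0% (factor odds ratio 1), 4.9% (1.5), 4.9% (2), 4.5% (3) and 4.0% (5). The Monte Carlo error is √(0.05 × 0.95/100,000) = 0.07 points.

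A direct check at odds ratio 3 agrees. The response rates in the two factor levels are 15.1% and 34.9%. The true-to-assumed variance ratio is [(0.151 × 0.849 + 0.349 × 0.651)/2]/(0.25 × 0.75) = 0.948. The error rate is then 2[1 − Φ(1.96/√0.948)] = 4.4%.

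**Step 6. Linear secondary models.** If the omitted factors explain a share R² of the residual variance, the reported SE is too large by a factor of about 1/√(1 − R²). Under assumed values this is 1.010 for R² = 2% and 1.026 for R² = 5%.

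**The case against.** The strongest reply is that these are wording slips with little behind them. The omitted factors are consents to optional sub-studies. The Recruitment section offers those sub-studies only at centres with ultrasound and biopsy facilities, so centre, which is in the models, already captures part of what consent reflects. Nothing in the article suggests that consent predicts a change in symptoms, and the primary model already carries both baseline scores. Leaving the consents out is a defensible choice. This stands as a reason not to adjust for them. It does not explain why three factors are labelled as if they were the full set, and it does not touch the two duration cuts.

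Four stronger readings are tempting, and the documents do not support them.

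- **Error rate.** A reader might infer that the mismatch inflates the type I error or biases the comparison. Step 5 shows the opposite direction, and only mildly. Recoding a few patients on one covariate does not in itself bias the treatment effect.
- **Wasted balance.** A reader might infer that the primary standard error is too large and that the balance is wasted. That reasoning fits the linear models. In the logistic model the adjusted SE is the larger one, and the loss is the small power difference in Step 4.
- **Patients misplaced.** A reader might take 3 to 9 of 110 patients as an estimate. It is arithmetic on an unsourced assumption, and the true number may be close to zero.
- **Uneven admission.** A reader might infer that sites will admit and refuse the same 10-year patient. The Screening section points to Table 1 for the criteria, and the differing phrase sits in a short list of who may be re-screened. The two wordings conflict, but nothing shows that sites acted differently.

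**Conclusion.** The mismatch is established by the text alone. Disease duration is cut on opposite sides of 10 years at allocation and in the primary model, two of five minimisation factors are absent from the listed covariates without a reason, and the secondary section mislabels three factors as the set.

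The consequence is small. Validity is not threatened, the type I error is not inflated, and no sample-size figure changes. The figures in Steps 4 and 5 rest on one exactly balanced binary factor with 50% prevalence and an assumed link to outcome. They shrink to nothing if the consent factors are not prognostic, which is quite possible. The correction is still worth making, because it makes the analysis match the design and removes discretion over the covariate set at almost no cost.

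**What to change.** 1. Code disease duration in the primary and secondary models as it was coded at minimisation, ≥10/<10 years.
2. Include biopsy consent and ultrasound consent in those models. If they are left out because they exist only to balance the sub-studies, say so and correct the label in Secondary outcome analyses, so that it no longer presents three factors as the full set. Either way, make the unlisted references in the later bullets point to one stated list.
3. Separately, reconcile the wording of the 10-year boundary in the Screening section with that of inclusion criterion 4. Which wording should prevail is for the trial team.

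The cost is a few words of analysis text, an eligibility clarification and at most two binary terms per model. The change should be fixed before unblinding.
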